### Trial treatment, data collection and analysis

#### Phase one: researcher review and evaluation of CGT apps in the marketplace

Collect and evaluate brain training apps from Google Play and the App Store. For the purpose of this study, brain training apps are operationally defined as mobile applications that provide non-invasive, readily accessible, and self-directed gamified cognitive tasks targeting various cognitive domains, including memory, attention, problem-solving, and processing speed^29^. These apps are designed to actively engage users with game-like exercises during dialysis sessions, encouraging them to independently practice their cognitive functions. The selection process will involve collecting and evaluating brain training apps available on Google Play and the App Store based on their adherence to this operational definition and their suitability for use in the haemodialysis setting at the unit.Shortlist apps based on their usefulness for cognitive training. While gaming apps may offer an accessible and engaging approach during haemodialysis sessions, it is important to note that their validity compared to standard cognitive assessments administered by trained professionals has not been established specifically in the haemodialysis population. Therefore, we will use validated cognitive assessment tools (MoCA, 3MSE) as our primary outcome measures, with the gaming apps serving primarily as an engagement tool during treatment sessions rather than a cognitive assessment instrument.All data collection and analysis in Phase one will be conducted by the investigators, without patient involvement.

These areas will guide the development of specific questions, which will be refined based on input from the research team and piloting with a small group of patients. This approach will ensure a comprehensive assessment of app usefulness while allowing flexibility to explore emerging themes during discussions. Focus groups/semi-structured interviews will be conducted by trained members of the research team, including study investigators and research assistants.

#### Phase two: assessment and selection of CGT apps for the main trial in conjunction with the kidney patient groups

Conduct focus groups/semi-structured interviews with haemodialysis patients to assess the usefulness of cognitive training apps during dialysis sessions.Collaborate with KPAs and Kidney Care UK representatives.The interview structure will be based on the Technology Acceptance Model (TAM^30^), which is widely used to evaluate user acceptance of new technologies. Key areas of inquiry will include:Perceived ease of use (e.g., How easy or difficult was it to use the app during dialysis? ).Perceived usefulness (e.g., In what ways might this app be beneficial during dialysis sessions? ).Attitude towards using (e.g., What are your overall thoughts on using this app during dialysis? ).Behavioural intention to use (e.g., How likely would you be to use this app regularly during future sessions? ).

#### Phase three: undertake CGT apps intervention in people receiving haemodialysis

Perform baseline assessments: Montreal Cognitive Assessment (MoCA), Modified Mini-Mental State Exam (3MSE), Rapid Objective Working Memory Assessment (ROWMA), Patient-Reported Outcomes Measurement (PROM) Kidney Disease Quality of Life Short Form (KDQoL-SF^™^) v 1.3, Patient-Reported Outcomes Measurement Information System (PROMIS) Global Health Instrument, European Quality of Life Five Dimension (EQ-5D) for cognitive function, quality of life, and well-being.The combination of cognitive assessments (MoCA, 3MSE, ROWMA) provides an evaluation of cognitive function, ranging from screening for mild impairment to specific assessment of working memory. For quality of life, the use of both disease-specific (KDQoL-SF™) and generic (EQ-5D, PROMIS) measures allows for an understanding of the intervention’s effects on QoL. This multi-faceted approach enhances the validity and reliability of our findings, capturing both general and kidney disease-specific aspects of cognitive function and quality of life that may be impacted by the intervention.In the intervention group, patients will use the selected CGT apps on tablet devices during haemodialysis sessions for a minimum of 30 min per session, 3 times per week, over the 4-month intervention period. The research team members will provide initial training on app use and will be available to assist patients as needed throughout the intervention. Regular check-ins with patients will be conducted to discuss their experiences and address any barriers to app use.In the control group, provide standard care.After four months, repeat assessments (MoCA, 3MSE, ROWMA, KDQoL-SF^™^, PROMIS, EQ-5D) and compare results between intervention and control groups.

Data collection and analysis will be conducted by investigators and trained study staff. Due to the nature of the intervention, blinding is not possible in this study. Participants will be aware of whether they are receiving the cognitive training intervention or standard care. Dialysis staff will also be aware of which patients are using the cognitive training apps during dialysis sessions. Additionally, outcome assessors cannot be blinded in this study design. The visible presence of tablets and app usage during dialysis sessions for the intervention group makes it impossible to conceal group allocation from the assessors.

We acknowledge that the lack of blinding at all levels is a limitation of our study design. This is a common challenge in studies of behavioural interventions in clinical settings, particularly those involving technology use during treatment. To mitigate potential bias despite the lack of blinding:

We will use standardized assessment protocols to ensure consistent data collection across all participants.Where possible, we will rely on objective measures (e.g., app usage data, standardized cognitive tests) to minimize subjective influences.Multiple assessors will be used to reduce individual bias.

We will thoroughly discuss this limitation and its potential implications in our final report, considering how it might impact the interpretation of our results.

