### Intervention timeline

The CGT intervention will be delivered during the first half of the haemodialysis session, typically within the first 1–2 h, to ensure that patients are alert and able to engage with the cognitive training. Regarding the study procedures:

Baseline assessments (questionnaires and cognitive tests) will be conducted in the week prior to starting the intervention.The intervention will last for four months (16 weeks ± two weeks).Patients will be asked to use the cognitive training apps for approximately 30 min during each haemodialysis session, 3 times per week.Post-intervention assessments will be conducted in the week following completion of the 16-week intervention.

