### Intervention implementation and practical considerations

Participants will be instructed to use their non-fistula/graft arm for interacting with the tablet during CGT to avoid any potential complications. All tablets will have stands to minimise arm movement if required.

Regarding the timing of dialysis shifts, we acknowledge that early morning shifts may pose challenges. To address this, we will ensure that the CGT apps are designed with adjustable brightness and volume settings to accommodate patient comfort at different times of day.

The involvement of dialysis staff will be minimal to ensure the intervention remains patient-led. Staff responsibilities will include:

Initial setup of tablets (performed by the research team).Providing tablets to patients at the start of their session.Basic troubleshooting if needed (e.g., restarting an app).Collecting tablets at the end of the session.

Staff will receive a brief training session on these responsibilities. We estimate this will require no more than 5–10 min of staff time per patient per session. The research team will be available to address any technical issues that arise.

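### Visible tablets during dialysis do not make assessor masking impossible, because each patient's MoCA and 3MSE are timetabled for weeks when that patient is not using a tablet

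*Protocol article*

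**What the plan says.** On masking, the Phase three section of the protocol article states: "Additionally, outcome assessors cannot be blinded in this study design". The reason follows at once: "The visible presence of tablets and app usage during dialysis sessions for the intervention group makes it impossible to conceal group allocation" from those assessors. No other reason is given for assessors. The text then concedes: "We acknowledge that the lack of blinding at all levels is a limitation of our study design". It lists three mitigations: standardised assessment protocols, objective measures where possible, and more than one assessor.

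On timing, the Intervention timeline states: "Baseline assessments (questionnaires and cognitive tests) will be conducted in the week prior to starting the intervention", and "Post-intervention assessments will be conducted in the week following completion of the 16-week intervention". The app period is 16 weeks, give or take two. Under Intervention implementation and practical considerations, tablets are handed out at the start of each session, and staff duties include "Collecting tablets at the end of the session".

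On allocation, the Randomisation section has the research team assign whole dialysis routes (six in all) to an arm. It does not say whether this happens before or after baseline testing. The Participant withdrawal and Outcomes sections give follow-up as about four months with a two-week margin either side, which is looser than the timeline.

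**The concern.** The article presents unmasked assessment as forced by the design. The one reason offered concerns what can be seen while patients are using the app, whereas the outcome tests are timetabled outside that period. If the reason does not hold, a safeguard has been given up without a sound argument.

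The MoCA and 3MSE depend on how a person administers and scores them, and both belong to the primary outcome, which is change from baseline. An assessor who knew the arm at both visits could lean low at baseline and high at four months in the intervention arm, and the two leans would add in the change score. None of the listed mitigations hides the arm. The pilot's effect estimates are meant to inform the sample size of a definitive trial (Statistical analysis), so any bias would carry forward.

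**Working it through.** **Step 1: does app use overlap the test weeks?** Count weeks from a patient's first app session, with an app period of length L. Take completion to mean the end of that patient's app period.

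- Baseline tests: week −1 to 0
- App use: week 0 to L
- Follow-up tests: week L to L + 1

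| L (weeks) | Follow-up tests | Overlap at baseline | Overlap at follow-up |
|---|---|---|---|
| 14 | 14 to 15 | 0 | 0 |
| 16 | 16 to 17 | 0 | 0 |
| 18 | 18 to 19 | 0 | 0 |

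Under the timeline, a patient's own tablet use cannot reveal the arm in either test week.

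**Step 2: does the looser window change this?** Four months is 4 × 365.25 / 12 / 7 = 17.4 weeks, so two weeks either side gives 15.4 to 19.4 weeks. If four months is read as 16 weeks, the window is 14 to 18. Either lower limit falls before the end of a 16-week app period. The looser wording, taken alone, would allow a follow-up test while the app is still in use. The timeline does not, so the sections need aligning.

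**Step 3: which outcomes are exposed?** MoCA and 3MSE are the person-scored tests. The article describes ROWMA as computerised, which leaves less room for assessor influence. The quality-of-life instruments are answered by patients who know their arm, so masking assessors would not protect them.

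**Step 4: hypothetical size.** The protocol gives no alpha, SD, power or bias figure, so there is no planned figure to reproduce. The assumptions are a true effect of zero, a two-sided 5% test, a normal approximation, independent patients (clustering by route ignored), and a net lean of b SD in the between-arm difference. With 25 completers planned in the intervention arm and 25 controls:

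SE = √(1/25 + 1/25) = 0.283 SD

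Rejection probability = P(Z > 1.96 − b/SE) + P(Z < −1.96 − b/SE)

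| Assumed lean b (SD) | Probability of p < 0.05 |
|---|---|
| 0 | 5.0% |
| 0.1 | 6.4% |
| 0.2 | 10.9% |
| 0.3 | 18.6% |

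**The case against.** The strongest reply is that the timeline is written per patient. The article does not say where tests take place or whether patients in a route start together. With staggered starts, route-mates could be using tablets during another patient's test week. Because a whole route shares one arm, a single remark or one visit to a shift could unmask the entire route. This stands. It means masking would be imperfect, and that the absence of tablets in a test week can be claimed only for the patient's own use. It does not rescue the article's reason, which is visibility during sessions alone.

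The limitation is also disclosed, with a commitment to discuss it, in a pilot aimed first at feasibility. That lowers the stakes, but disclosure does not make the stated impossibility correct.

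Four stronger readings are tempting and are not supported:

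- **Arm knowledge does enter the baseline scores.** No section places route allocation before baseline testing; Regulatory aspects requires only that consent come before randomisation and study procedures. Knowledge of the arm at baseline is possible, not stated.
- **The analyst must also be unmasked.** The concession about all levels most naturally refers to the participants, dialysis staff and assessors just named. Coding the arm for analysis is commonly left to a document not shown here.
- **Masking would be free.** The research team sets up tablets, trains and assists patients and decides allocation. Planning several assessors does not show that any of them stands apart from those duties.
- **The false-positive rates predict what will happen.** The lean is assumed, the protocol sets no significance level, and the Outcomes section words the primary outcome as change within the intervention group, whereas the calculation uses a between-arm contrast.

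**Conclusion.** The point holds in limited form. The only reason given for unmasked assessors does not support the claim of impossibility, because under the article's own timeline a patient's app use overlaps neither test week (0 weeks for app periods of 14, 16 or 18 weeks). The result is an avoidable risk of bias, mainly in MoCA and 3MSE; the documents do not show that bias has occurred or will occur. Its size cannot be derived from them, and the range of 6.4% to 18.6% is purely hypothetical under the assumptions listed above. The conclusion rests on the Intervention timeline governing follow-up rather than the looser window. Full masking is not assured, but partial masking is achievable and better than none. The change should be made, though the pilot does not stand or fall on it.

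**What to change.** Replace the statement that assessors cannot be blinded with two provisions:

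1. Complete the baseline tests in a route before that route's arm is decided or disclosed.
2. At four months, where rostering of the several assessors already planned allows, have MoCA and 3MSE given by assessors who took no part in tablet set-up, training or check-ins. They should not hold the route-to-arm list and should test away from sessions where tablets are in use. Ask patients not to mention the app, and record each assessor's guess of the arm.

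Also align the two-week margin in Participant withdrawal and Outcomes with the Intervention timeline, so that follow-up tests clearly fall after app use ends.

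The cost is sequencing, rostering and a few small added procedures. Since baseline is tied to the week before app use, the first provision requires more synchronised starts within a route. Because whole routes share an arm, some unmasking will remain. Report it as a limitation, using the recorded guesses to show its extent, alongside the unmasked patients and dialysis staff.

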### Outcomes

The primary outcome will be a change in cognitive test results (MoCA, 3MSE and ROWMA) of the intervention group at approximately four-month (± two weeks) follow-up assessments compared to the baseline assessments. The secondary outcomes will be the change in the behavioural test scores (PROM KDQoL-SF™ v1.3, PROMIS Global Health Instrument and EQ-5D questionnaires) for the CGT intervention group compared to the control group. The following validated instruments will be used to assess cognitive function, quality of life, and general health and well-being:

MoCA: A sensitive screening tool for mild cognitive impairment, assessing various cognitive domains including attention, concentration, executive functions, memory, language, visuoconstructional skills, conceptual thinking, calculations, and orientation^31^.3MSE: An expanded version of the MMSE that provides a comprehensive and sensitive measure of global cognitive function^32^.ROWMA: A brief, computerised test specifically designed to assess working memory, which is often impaired in patients with kidney disease^33^.KDQoL-SF™: A kidney disease-specific measure of health-related quality of life that includes generic core plus disease-specific domains such as symptom/problems, effects of kidney disease on daily life, burden of kidney disease, cognitive function, and dialysis staff encouragement^34^.PROMIS Global Health Instrument: A brief, generic self-report measure of health-related quality of life that assesses physical, mental, and social health^35^.European Quality of Life 5-D (EQ-5D): A standardized instrument for measuring generic health status, providing a simple descriptive profile and a single index value for health status^36^.

Table 2 provides a summary of these assessment tools, including their functions, score ranges, administration details, and other relevant information.

**Table 2 Tab2:** Summary of assessment tools.

Assessment tool	Function/rationale	Score range and interpretation*	Administration timing	Time to complete	Other details
Montreal Cognitive Assessment (MoCA)	Screens for mild cognitive impairment	0–30; ≥26 normal	Baseline and 4 months	10–15 min	Assesses multiple cognitive domains
Modified Mini-Mental State Exam (3MSE)	Comprehensive measure of global cognitive function	0-100; higher scores indicate better cognitive function	Baseline and 4 months	10–15 min	More sensitive than standard MMSE
Rapid Objective Working Memory Assessment (ROWMA)	Assesses working memory	Scores vary; higher scores indicate better working memory function	Baseline and 4 months	5–10 min	Computerised test
Kidney Disease Quality of Life Short Form (KDQoL-SF™)	Kidney disease-specific quality of life measure	0-100 for each subscale; higher scores indicate better quality of life	Baseline and 4 months	10–15 min	Includes generic and kidney disease-specific components
PROMIS Global Health Instrument	Brief measure of general health-related quality of life	T-score metric (mean = 50, SD = 10); higher scores indicate better health	Baseline and 4 months	5–10 min	Assesses physical, mental, and social health
European Quality of Life 5-D (EQ-5D)	Generic measure of health status	Index value 0–1; higher scores indicate better health status	Baseline and 4 months	5–10 min	Provides health utility scores for economic evaluations

*Score ranges and interpretations are based on general population normative data unless otherwise specified. Specific cutoff values and interpretations for the haemodialysis population may differ and are currently not well established. This highlights the exploratory nature of using these assessment tools in our specific.

Examining and comparing the cognitive and behavioural test scores of the intervention and control groups at the four-month assessments will provide insight to expand the scope and area of CGT intervention to other haemodialysis units. Feasibility outcomes will include patient recruitment and retention rates, adherence to the intervention (app usage frequency and duration), and the occurrence of any technical issues or adverse events. Acceptability will be assessed through semi-structured interviews with a subset of intervention group participants, exploring their experiences, satisfaction, and perceived benefits and challenges of using the CGT apps. If the feasibility and acceptability of CGT intervention are demonstrated, we will apply for further funding so that the CGT intervention can be delivered to more people receiving haemodialysis.

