## Abstract

Disruptions in cognitive function have been reported in individuals undergoing haemodialysis and those with chronic kidney disease. This pilot study protocol primarily assesses the feasibility and acceptability of using mobile cognitive gaming apps for patient-led cognitive training during haemodialysis sessions. The protocol consists of three phases: (1) reviewing and evaluating available cognitive gaming apps, (2) conducting focus groups/interviews with people with kidney disease to determine app preferences, and (3) undertaking a quasi-experimental randomised controlled trial to compare cognitive outcomes between a patient-led app intervention group and a standard care control group over four months. Primary outcomes will include changes in cognitive test scores [Montreal Cognitive Assessment (MoCA), Modified Mini-Mental State Exam (3MSE), Rapid Objective Working Memory Assessment (ROWMA)], while secondary outcomes will encompass quality of life measures [Patient-Reported Outcomes Measurement (PROM) Kidney Disease Quality of Life Short Form (KDQoL-SF™) v 1.3, Patient-Reported Outcomes Measurement Information System (PROMIS) Global Health Instrument, European Quality of Life Five Dimension (EQ-5D)]. If demonstrated to be effective, this novel method of utilising gamified cognitive training applications could potentially mitigate cognitive decline and improve the well-being of people receiving haemodialysis without necessitating significant clinical resources. The findings from this research will guide the development of a larger definitive randomised trial in the future.

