### Statistical analysis

Given the pilot nature of this study, our sample size is not based on formal power calculations. Instead, it is pragmatically determined by the number of eligible patients in our dialysis unit. The results will be used to estimate effect sizes and inform sample size calculations for a future, full-scale randomised controlled trial.

In Phase three, data will be analysed to test the effect of CGT intervention on the scores of baseline and follow-up assessments. All data analyses will be conducted in IBM SPSS Statistics for Windows, version 27.0 (or higher) software. Data will be directly entered into Microsoft Office Excel spreadsheets (version 2202) by investigators and study staff using all standard data management procedures. Descriptive statistics will be calculated according to the normality assumption, with means and standard deviations reported for normally distributed data, and medians and interquartile ranges reported for non-normally distributed data. Within-group comparisons between baseline and follow-up assessments for primary and secondary measurements will be analysed using repeated-measures analysis of variance (ANOVA). In contrast, independent ANOVA will be used for between-group comparisons. For additional explorative analyses, correlation and regression models can be used to analyse the effects of other factors (e.g. age, gender) on the cognitive decline between the baseline and follow-up assessments.

In addition to the primary and secondary outcome analyses, a sub-group analysis will be performed to explore the potential effects of the CGT intervention based on participants’ baseline memory function and executive function. Participants will be stratified into subgroups based on their performance on the cognitive test scores, and the intervention effects will be compared between these subgroups. This exploratory analysis may help to identify which patients are most likely to benefit from the CGT intervention and guide future research in this area.

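### The article disagrees with itself on which cognitive tests are primary and names no lead score, so the result carried to the definitive trial can be chosen after the data are seen.

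*Protocol article*

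**What the plan says.** **Which tests are primary.** The Outcomes section states: "The primary outcome will be a change in cognitive test results (MoCA, 3MSE and ROWMA"), for the intervention group, measured at about four months against baseline. The Abstract agrees on the set but uses the plural: "Primary outcomes will include changes in cognitive test scores", followed by the same three instruments. The section on Phase one (review of apps) gives a shorter list. It names MoCA and 3MSE as the primary outcome measures and does not mention ROWMA.

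**Scales.** Table 2 gives MoCA as 0 to 30 and 3MSE as 0 to 100. For ROWMA it says only that scores vary. No composite is described.

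**Analysis.** The Statistical analysis section says that in Phase three "data will be analysed to test the effect of CGT intervention on the scores of baseline and follow-up assessments". It continues: "Within-group comparisons between baseline and follow-up assessments for primary and secondary measurements will be analysed using repeated-measures analysis of variance (ANOVA"), with independent ANOVA for the comparison between groups. It does not say which of the two analyses answers the primary question.

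**Purpose.** The Trial design section speaks of assessing feasibility and effectiveness. The recruitment and Statistical analysis sections call the study a pilot without a power calculation, whose results will supply effect sizes and sample-size inputs for a later trial.

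**The concern.** Three instruments that range from a screening test to a specific working-memory task can give different answers. The article offers no lead score, no ordering and no statement of whether one, two or all three must move. Whether ROWMA belongs to the primary set cannot be settled from the text, because two sections include it and one leaves it out.

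Two things are at stake. First, a single nominally significant test could be reported as an effect while the other tests show nothing. Second, and more important for a pilot, the score whose effect size and standard deviation feed the next sample-size calculation is open to choice after the results are known. The largest of several noisy estimates is, on average, too large.

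**Working it through.** The article gives no significance level, power or error rate on this point, so there is no stated figure to reproduce. The inputs below are assumptions unless a source is named.

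**1. The primary set, section by section**
- Abstract: MoCA, 3MSE, ROWMA.
- Outcomes: MoCA, 3MSE, ROWMA, as change within the intervention group.
- Phase one section: MoCA, 3MSE.
- Trial design and Phase three sections: intervention compared with control.

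The sections conflict on the number of primary tests (two or three) and on the contrast (within one arm or between arms).

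**2. False-positive chance if any one test counts**

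Assume 5% two-sided per test, one contrast per test, no true effect and an equal correlation ρ between the test statistics. For independent tests the chance is 1 − 0.95³ = 0.1426, and 0.1426 / 0.05 = 2.85. For ρ > 0, the chance is 1 − P(all |Z| < 1.96) for equicorrelated normals, by numerical integration.

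| ρ | Three tests | Multiple of 5% |
|---|---|---|
| 0 | 14.3% | 2.85 |
| 0.3 | 13.6% | 2.72 |
| 0.5 | 12.5% | 2.51 |
| 0.7 | 10.9% | 2.18 |
| 0.8 | 9.8% | 1.96 |
| 0.9 | 8.4% | 1.67 |

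With the two tests of the Phase one section, the multiple is 1.95 if independent (1 − 0.95² = 0.0975) and 1.81 at ρ = 0.5. If all three tests had to be significant in the same direction, the chance would be 0.3% at ρ = 0.5. The reading that is left open therefore matters in both directions.

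**3. Excess from carrying the largest estimate forward (illustration)**

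Assume 25 completers per arm, the number that the article aims for in the intervention arm and recruits in the control arm. Assume also equal true standardised effects on the three tests and independent patients.
- Standard error of a standardised difference: √(2/25) = 0.28.
- Expected maximum of three independent standard normals: 0.846.
- Expected excess of the largest estimate: 0.846 × √(1 − ρ) × 0.28.
- Result: about 0.24 SD at ρ = 0, 0.17 SD at ρ = 0.5 and 0.11 SD at ρ = 0.8.

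If the true effect were 0.30 SD (assumed), planning at ρ = 0.5 would use 0.30 + 0.17 = 0.47 SD. Required size goes with 1/effect², so the definitive trial would have (0.30/0.47)² ≈ 0.41 of the patients it needs. Whole dialysis routes are allocated to an arm, so outcomes that are alike within a route would increase the standard error and with it the excess.

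**The case against.** The strongest reply is that this is a pilot. The Statistical analysis section says that the main goal is initial data and a check of procedures, not a powered hypothesis test. The Outcomes section ties the next funding application to feasibility and acceptability, not to a significant cognitive result. Only an article is shown, so a significance level and a multiplicity adjustment may stand in an analysis plan.

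Much of this stands, and it rules out several stronger readings that a reader might infer:
- **That the plan has a false-positive rate about 2.5 times nominal.** That figure needs a 5% level, a correlation near 0.5 and a rule that any one positive test counts. The article states none of these.
- **That the lack of a multiplicity adjustment is itself a defect.** An article commonly leaves this to the analysis plan.
- **That the secondary outcomes have the same fault because KDQoL-SF is scored by subscale.** The choice of subscale may also be made in the analysis plan.
- **That the Phase three remark "This multi-faceted approach enhances the validity and reliability of our findings" is a statistical error.** Its sentence goes on to describe breadth of coverage and makes no claim about error rates.

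The reply does not remove the core. The article itself names the primary outcome, and does so inconsistently, so this is not a matter of condensed detail. The same section that disclaims powered testing also says that the effect will be tested. And the stated use of the results, to inform a later sample size, is the use that a score chosen after the fact would harm.

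**Conclusion.** The point holds in a limited form. The Abstract and Outcomes sections make three cognitive tests primary and the Phase one section makes two. No section names a lead score or says how discordant results are read. The analysis wording would let any one of them be presented as an effect, although the article does not say that it will be.

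Under that reading, and at an assumed 5% two-sided level, the false-positive chance over three tests is about 8% to 14% for correlations from 0.9 down to 0. This counts one contrast per test. Using both the within-group and the between-group analysis would raise it.

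The more relevant size for a pilot is the upward bias of a score chosen after the fact: about 0.11 to 0.24 SD for correlations from 0.8 down to 0, with 25 independent completers per arm and equal true effects. These figures show the order of magnitude. They are not estimates for this trial, since the article gives neither the correlations nor the standard deviations.

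**What to change.** 1. **Abstract, Phase one and Outcomes sections:** state the same primary set in all three.
2. **Outcomes:** before data are seen, name one lead cognitive score. MoCA and 3MSE are both described as validated primary measures and both have a fixed scale in Table 2, so the choice between them is the sponsor's. Make the remaining tests supportive.
3. **Outcomes:** say openly that the lead score is compared between intervention and control, and that this replaces the change within the intervention group now written there. This is a change of contrast, not only of wording, but it matches the comparison already described in the Trial design and Phase three sections.
4. **Statistical analysis:** replace the statement about testing the effect with estimates and confidence intervals for all scores. State that no claim of effect will rest on one isolated result, and that the definitive trial will be sized from the named score.

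The cost is text in four sections, with the same patients, visits and instruments. The downside is that an isolated positive result on a supportive test can no longer be presented as a primary effect.
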